## 5.5 Serum Sample Randomization and Blinding

All serum samples sent to analysis laboratory will be under the blinded matter. On the serum samples used for antibody titrations there will be no information available regarding subject background data (e.g., age, pre- or post-serum). The serum will be re-labeled with serum number according to the randomization list for serum samples before being sent to the analysis laboratory. For each subject, there will be four randomization numbers allocated, one for the pre-vaccination serum sample (Visit 1), one for the post-vaccination serum sample (Visit 2, Week 4), one for the end of gestation period (Visit 3, delivery) serum sample from maternal subject (within 8 weeks after delivery) and one for the cord blood sample (Visit 3).

## 6. ADVERSE EVENTS

All reported adverse events within 4 weeks after the vaccination will be recorded as much as possible. Adverse event during the 30-minute observation period after the vaccination will be collected on site. Reactogenicity within the first 7 days after the vaccination will be recorded in the diary card. Specific adverse events of interest, i.e., Guillain-Barre syndrome, anaphylaxis, convulsions, encephalomyelitis, central nervous system demyelinating diseases, Bell's palsy and vasculitis, will also be recorded in the CRF. Moreover, influenza, pneumonia, heart failure, stroke, exacerbation of chronic pulmonary disease and other respiratory illness with fever will also be recorded.

The term "adverse event" covers any sign, symptom, syndrome or illness that appears or worsens and is not of benefit to the subject during the period of observation in a clinical study. The term also covers laboratory findings (if applicable) or the results of other diagnostic procedures considered to be clinically relevant which:

- require additional diagnostic procedures not provided for in the study protocol
- require additional treatment measures not provided for in the protocol, or
- result in withdrawal of the subject from the study.

A study-emergent adverse event is defined as any event not present prior to signing informed consent or any event already present, which worsens in either intensity or frequency after signing informed consent. A treatment-emergent adverse event is defined as any event not present prior to exposure to study vaccine or any event already present, which worsens in either intensity or frequency following exposure to study vaccine.

The investigator is responsible for reporting all study-emergent serious adverse events and all treatment-emergent non-serious adverse events. If there is any doubt as to whether a clinical observation is a study or treatment-emergent adverse event, the event should be reported.

All adverse experiences must be rated on a 3-point scale of increasing severity, which defined as below:

Mild: Symptom barely noticeable to subject; does not influence performance or functioning. Prescription drug not ordinarily needed for relief of symptom but may be given because of personality of subject.

**Moderate:** Symptom of a sufficient severity to make subject uncomfortable; performance of daily activities influenced; subject is able to continue in study; treatment for symptom may be needed.

**Severe:** Symptom causes severe discomfort. May be of such severity that subject cannot continue the study. Severity may cause cessation of treatment with test drug; treatment for symptom may be given and/or subject hospitalized.

**Baseline medical condition:** It is not necessary to complete an adverse event form for adverse medical conditions present at baseline, which do not worsen in either intensity or frequency during the study. These adverse conditions should be adequately documented in the case report form and any other appropriate ancillary documents. Adverse medical conditions present at baseline, which become worse following exposure to study vaccine, should have an adverse event record completed.

**Reactogenicity:** events are pre-specified adverse events systematically recorded on diary cards (a grid of check boxes for each event and each day) during the immediate post-vaccination period by all participants. In general, reactogenicity events will be recorded for 7 days. The selection of the events to be collected systematically is based on events expected to occur with wild-type influenza infection. The events include fever ( $\geq 38^{\circ}\text{C}$ ), runny nose or nasal congestion, cough, sore throat, muscle aches, headache, vomiting, nausea and malaise. Furthermore, the local (injection site) reactions will also be evaluated that include soreness/pain, swelling, redness, ecchymosis and limitation of arm motion.

**Serious adverse events:** An adverse event which meets one or more of the following criteria is considered serious and must be reported in an expedited fashion:

- Results in death
- Is life-threatening
- Requires subject hospitalization or prolongation of existing hospitalization
- Results in persistent or significant disability/incapacity
- Is a congenital anomaly/birth defect
- Is medically important

Subjects experience the following events during the gestation period will also be reported as an serious adverse events: Guillain-Barre syndrome, anaphylaxis, convulsions, encephalomyelitis, central nervous system demyelinating diseases, Bell's palsy, vasculitis,

influenza, pneumonia, heart failure, stroke, exacerbation of chronic pulmonary disease and other respiratory illness with fever.

**Deaths:** In general, death should not be reported as an event. Death is viewed as an outcome of an event, rather than an event itself. In cases where the cause of death is unknown, “death” may be reported as an event on an initial serious adverse event form. However, every attempt should be made to submit a follow-up serious adverse event form identifying the probable cause of death when sufficient data are available.

**Documentation process:** All serious adverse events will be documented on a Serious Adverse Event forms, which will be completed by the study monitor with information provided by the investigator/study site. A copy of the Serious Adverse Event form will be filed with the subject’s case report form. All non-serious treatment-emergent adverse events will be reported in the case report form, which will be completed by the investigator/study site and are included in the subject’s case report form.

All serious adverse events, whether or not deemed vaccine-related or expected, during the study must be reported to designated representative immediately or within 24 hours (one working day) by telephone, telefax or electronic transmission.

A written report from the Investigator must be provided to the designed representative within 3 working days and is to include a full description of the event and sequel AE. This includes serious adverse events that occur anytime while enrolled in the trial. Written reports of all unexpected vaccine-related serious adverse events or authority-required serious adverse events must be submitted to the health authority and IRB in the hospital according to the regulated schedule of the health authority. Copies of each report will be kept in the investigator’s files, and adequate documentation notified of each serious adverse event.

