### **2.2 Secondary Objective**

The secondary endpoint is to evaluate the incidence rate of pre-specified adverse events and all serious/non-serious adverse events.

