### **2.3 Outcome Measure**

- Number of participants with seroprotection against influenza A/H1N1, A/H3N2, B virus (Day 28, the end of gestation period).
- Number of participants with seroconversion against influenza A/H1N1, A/H3N2, B virus (Day 28, the end of gestation period).
- Geometric means of post- to pre-vaccination antibody titer ratios against influenza A/H1N1, A/H3N2, B virus (Day 28, the end of gestation period).
- Number of participants reporting solicited subjective local reactions within 7 days (Day 1-7) post vaccination.
- Number of participants reporting solicited subjective systemic reactions within 7 days (Day 1-7) post vaccination.

- Number of participants reporting maternal complications of pregnancy, labor and delivery.
- Number of participants reporting neonatal complications.
- Number of participants reporting vaccine-associated serious adverse events (SAEs) during the study.

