### **3. STUDY DESIGN**

#### **3.1 Study Design**

This is a prospective, single-arm, descriptive clinical study to observed the safety and immunogenicity profile of the use of AdimFlu-S (2011-2012 season) vaccine in pregnant female subjects. All eligible participates will receive one dose of vaccine (0.5 mL) by intramuscular injection into the upper arm. Blood serum prepared from blood samples will be collected from each maternal subject immediately prior to vaccination and 4 weeks after vaccination; moreover, blood sample at the end of the gestation period (delivery) and the cord blood sample will also be collected, if applicable. Anti-hemagglutinin (HA) antibody titers will be determined using the WHO hemagglutination inhibition reference technique and the analysis will be observer-blinded. Safety outcomes included immediate reactions at the time of vaccination, solicited local and systemic reactions for 7 days, unsolicited adverse events until the first post-vaccination serum collected, and serious adverse events and adverse events of special interest until 8 weeks after the delivery.

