## **7.5 Analysis of Safety**

The safety end points are the frequency, duration, and intensity of solicited adverse events during the 7 days after each vaccination and the incidence of serious adverse events during the study period.

The Medical Dictionary for Regulatory Activities (MedDRA) Terminology will be used to classify all adverse events with respect to System Organ Class (SOC) and preferred term. In the case of severity and relationship summaries, the most severe event and the most directly related event will be presented in summary tables in the case of multiple occurrences per subject.

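### The SAE count includes designated events during gestation without a seriousness test, and Section 2.3 uses a different SAE numerator from Sections 2.2 and 7.5

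*Protocol*

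**What the plan says.** **Protocol Section 6 (serious adverse events).** The general rule is: "An adverse event which meets one or more of the following criteria is considered serious and must be reported in an expedited fashion". Six criteria follow: death, threat to life, hospitalization, disability, congenital anomaly and medical importance. The section then adds: "Subjects experience the following events during the gestation period will also be reported as an serious adverse events". The added list begins with neurological and allergic conditions and ends with "influenza, pneumonia, heart failure, stroke, exacerbation of chronic pulmonary disease and other respiratory illness with fever". It does not require any of the six criteria to be met.

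**Sections 3.1, 5.3 and 5.4.** Adverse events of special interest are named beside SAEs as a second class, and both are followed to the same point: "serious adverse events and adverse events of special interest until 8 weeks after the delivery". Section 5.3 places the respiratory and cardiac events, and stroke, in that special-interest class. For influenza it asks only for a positive test.

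**Which SAEs are counted.** The wording differs between three sections:
- Section 2.2: "the incidence rate of pre-specified adverse events and all serious/non-serious adverse events"
- Section 2.3: "Number of participants reporting vaccine-associated serious adverse events (SAEs) during the study"
- Section 7.5: "the incidence of serious adverse events during the study period"

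**The concern.** There are two linked problems.

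First, Section 6 gives SAE status to designated events because they are on a list, and only while the woman is pregnant. Test-positive influenza managed at home counts as an SAE the day before delivery. The week after delivery it is a special-interest event unless it meets a criterion. Section 7.5 pools both periods into one incidence, so that figure mixes two definitions.

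Second, the listed outcome measure in Section 2.3 has a narrower numerator than the secondary endpoint and the analysis section. Section 6 gives a severity scale but no criteria for calling an event vaccine-associated, and every subject is known to be vaccinated. The narrower count therefore rests on site judgement without a stated rule.

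Safety is the secondary objective. A reader of the results would need to know which of these counts the SAE incidence is, and the protocol supports more than one answer.

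**Working it through.** The protocol states no SAE rate and bases no sample size on SAEs, so there is no figure to reproduce. The check is a comparison of sections, followed by the arithmetic that n = 60 allows.

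**Step 1. Status of one illness, for example test-positive influenza with no hospitalization**

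| Timing | Meets a criterion in Section 6 | Meets none |
|---|---|---|
| During gestation | SAE | SAE, by the added list |
| Delivery to 8 weeks after | SAE | Special-interest event only |

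The right-hand column changes at delivery; the middle column does not.

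**Step 2. Three SAE counts follow from the text**

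- (a) Events meeting one of the six criteria.
- (b) Those in (a) plus every listed event during gestation. This is what Section 7.5 reports if Section 6 is applied as written.
- (c) Vaccine-associated SAEs only (Section 2.3).

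Both (a) and (c) are subsets of (b).

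There is also an overlap with reactogenicity. Fever, cough and sore throat are solicited on the diary for 7 days. Fever with cough in that week could be entered as a solicited reaction and also as a febrile respiratory illness, and so as an SAE.

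**Step 3. Sensitivity at n = 60 (Section 3.2)**

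One subject is 1/60 = 1.7 percentage points. Exact (Clopper-Pearson) 95% intervals:

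| Subjects with an SAE | Incidence | 95% CI |
|---|---|---|
| 0/60 | 0% | 0 to 6.0% |
| 3/60 | 5.0% | 1.0 to 13.9% |
| 6/60 | 10.0% | 3.8 to 20.5% |
| 9/60 | 15.0% | 7.1 to 26.6% |

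**Step 4. Illustration with assumed rates**

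Let s be the probability of an SAE by the six criteria, and f the probability of a listed gestational event meeting none of them. Both are assumptions, treated as independent. The expected number of subjects under (b) is 60 × [1 − (1 − s)(1 − f)]; under (a) it is 60 × s.

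With s = 5%, count (a) is 60 × 0.05 = 3.0. Count (b) is:
- f = 2%: 60 × (1 − 0.95 × 0.98) = 4.1
- f = 5%: 60 × (1 − 0.95 × 0.95) = 5.9
- f = 10%: 60 × (1 − 0.95 × 0.90) = 8.7
- f = 20%: 60 × (1 − 0.95 × 0.80) = 14.4

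That is 1.4 to 4.8 times count (a). Over s = 2% to 10% and f = 2% to 20%, the ratio runs from about 1.2 (s = 10%, f = 2%: 7.1/6.0) to 10.8 (s = 2%, f = 20%: 13.0/1.2). The width of this range shows that the protocol does not determine the size.

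**The case against.** The strongest reply is that the added list in Section 6 is a reporting rule, and that its events could fall under the sixth criterion, medical importance. Designating events for expedited reporting is legitimate and should stay. But nothing in the protocol keeps these events out of the Section 7.5 incidence, and medical importance does not explain why the status lapses at delivery. The reply does show that a fix that merely cites the six criteria would let the listed events back in through the sixth.

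A second reply is that MedDRA coding lets the designated events be picked out, and that table layout belongs to the statistical analysis plan. Both are true. The definition of the endpoint and the conflict between Sections 2.2, 2.3 and 7.5 are nevertheless in the protocol itself.

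A third reply is that the study is single-arm and descriptive, with no SAE threshold, hypothesis or external comparison. This stands and limits the consequence to how one descriptive result is defined and read.

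A reader might infer more than the documents support:
- **That the total is suppressed or filtered to near zero by attribution.** It is not. Sections 2.2 and 7.5 keep the unfiltered count, Section 6 requires SAEs to be reported whatever their relation to the vaccine, and Section 7.5 foresees relationship summaries. The Section 2.3 count can stand as a subset.
- **That an event after delivery cannot be an SAE.** It can, if it meets a criterion; otherwise the special-interest events are still followed to 8 weeks.
- **That dependence on remaining gestation comes from the added list alone.** Entry is open from 3 months of pregnancy and follow-up ends 8 weeks after delivery, so observation time varies under any definition.

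**Conclusion.** The point holds as an inconsistency in how the SAE endpoint is defined. As written, the Section 7.5 incidence combines criteria-based SAEs with designated gestational events that need meet no criterion, and the rule changes at delivery. The outcome measure in Section 2.3 has a different numerator from Sections 2.2 and 7.5. Both follow from the text without any assumption.

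The direction is also fixed by the text: the added list can only raise the count above the criteria-based one, and the relatedness filter can only lower it. The size is not fixed. Each affected subject moves the incidence by 1.7 points, but how many would be affected depends on rates the protocol does not give. It would be tempting to conclude that the SAE rate will be inflated several-fold by mild illness; that rests wholly on assumed rates, and some listed events would meet a criterion anyway. No data are lost at collection.

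**What to change.** Leave the expedited reporting of designated events in Section 6 unchanged, and revise the endpoint wording:

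1. In Sections 2.3 and 7.5, state one SAE endpoint: all-cause, over the full follow-up to 8 weeks after delivery, counting events assessed case by case as meeting a listed seriousness criterion. Say that being on the designated list does not by itself make an event medically important.
2. Tabulate the designated events separately over the same full follow-up, so that the table does not change definition at delivery.
3. Report vaccine-associated SAEs as a subset of the all-cause total.

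The cost is wording in two sections, one extra table, and a record of which seriousness criterion each SAE met. Differences in observation time between women will remain.

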## **7. STATISTICAL ANALYSIS**

### **7.1 Sample Size Consideration**

This is a descriptive study based on the use of 95% confidence intervals (CI), the sample size calculation is based on the expected precision of the results (extent of the 95% CI) and on the European recommendations for studies evaluating influenza vaccines to be used during each

influenza season (at least 50 subjects per group). Therefore, 60 maternal subjects are planned to be recruited.

For establishing the acceptability of the antibody response to H1N1, H3N2, and B for AdimFlu-S, the seroconversion rates for H1N1, H3N2, and B in the subjects receiving AdimFlu-S will be tested against a 40% lower bound for adult subjects.

According to the previous result, in the season of 2010-2011, the non-pregnant female (aged between 20 and 40) had the seroconversion rates were 84.6% against influenza A/H1N1 virus, 80.8% against influenza A/H3N2 virus and 38.5% against influenza B virus. Given 60 female subjects who receive AdimFlu-S will be evaluable for antibody titers, this study has at least 99% power to establish an acceptable seroconversion for A/H1N1 and A/H3N2, and 4.46% for B with 5% two-sided significance level.

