### **2.1 Primary Objective**

- To evaluate the immune response of the three vaccine viral strains by calculation of the geometric mean titers (GMT) of anti-HA antibodies, geometric means of post- to pre-vaccination antibody titer ratios, seroprotection rates, and seroconversion rates.

The primary endpoint will be the seroprotection rate which is defined as the proportion of subjects with HAI titer  $\geq 1:40$ . The other immunogenicity endpoints include seroconversion rate and geometric mean folds increase in HAI titer. Immunogenicity profile will be assessed before vaccination, 4 weeks after the vaccination and at the end of gestation period.

Moreover, the HAI titer of the cord blood will also be measured and compared with the maternal blood sample.

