## **7.4 Analysis of Immunogenicity**

The immune response to the three vaccine viral strains is assessed by calculation of the geometric mean titers (GMT) of anti-HA antibodies, geometric means of post- to pre-vaccination antibody titer ratios (GMTR, with 95% confidence intervals), seroprotection rates (percentage of subjects with a titer  $>1:40$  at 4 weeks after vaccination and at the end of gestation period), seroconversion rates. The seroconversion rate is defined as the percent of subjects with a pre-vaccination titer  $< 1:10$  achieving a titer  $\geq 1:40$  or with pre-vaccination titer  $\geq 1:10$  having at least a four-fold rise at 4 weeks after vaccination and at the end of gestation period. As for the rate of seroprotection and seroconversion rate, the 95% exact (Clopper-Pearson) confidence interval will be provided as well.

European Agency for the Evaluation of Medicinal Products/Committee for Proprietary Medicinal Products (CPMP) immunogenicity criteria for licensed influenza vaccines specifies 70% seroprotection or 40% seroconversion, or a GMTR of 2.5 for individuals between 18 and 60 years of age.[12]

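### The primary endpoint is seroprotection, but the only test and power are for seroconversion, and the role of the any-of-three European criterion is left unstated

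*Protocol*

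**What the plan says.** **Primary endpoint.** Section 2.1 states: "The primary endpoint will be the seroprotection rate which is defined as the proportion of subjects with HAI titer" at least 1:40. It continues: "The other immunogenicity endpoints include seroconversion rate and geometric mean folds increase in HAI titer". Section 2.1 attaches no threshold to any of these.

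**Test and power.** Section 7.1 calls the study descriptive. It bases the sample size on the expected extent of the 95% confidence interval and on a European recommendation of at least 50 subjects per group. It then says that, to establish acceptability, the seroconversion rates for the three strains "will be tested against a 40% lower bound for adult subjects". The assumed seroconversion rates are "84.6% against influenza A/H1N1 virus, 80.8% against influenza A/H3N2 virus and 38.5% against influenza B virus". The power statement begins "Given 60 female subjects who receive AdimFlu-S will be evaluable for antibody titers" and goes on: "this study has at least 99% power to establish an acceptable seroconversion for A/H1N1 and A/H3N2, and 4.46% for B" "with 5% two-sided significance level". Section 7.1 gives no null value, power or interval width for seroprotection.

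**European criterion.** Section 7.4 plans exact (Clopper-Pearson) 95% intervals for both rates. It then reports that the CPMP criteria for licensed influenza vaccines "specifies 70% seroprotection or 40% seroconversion, or a GMTR of 2.5 for individuals between 18 and 60 years of age". It does not connect this to the test in 7.1 or to the primary endpoint in 2.1.

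**Cut-off.** Section 2.1 defines seroprotection as a titer of at least 1:40; the definition in 7.4 uses strictly above 1:40.

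**The concern.** A reader who looks for the basis on which the vaccine will be called acceptable in pregnant women finds a primary endpoint in one section and a test of a different endpoint in another. The power figures in 7.1 cannot be used to judge whether 60 women are enough for the primary endpoint. The confidence-interval precision that 7.1 names as the basis of the sample size is not given for it either.

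The quoted any-of-three criterion adds a second uncertainty. If it were used to decide, a strain could be declared acceptable on its fold rise alone, even if it failed both the primary endpoint and the tested endpoint. The earlier data in Section 1 show that strain B is likely to be in exactly that position, so the gap could change the conclusion for one of three strains.

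**Working it through.** **Inputs**
- n = 60 evaluable, null value 40%, two-sided 5% level: Section 7.1.
- Seroconversion rates 84.6% (H1N1), 80.8% (H3N2), 38.5% (B): Section 7.1.
- Seroprotection rates 92.3%, 88.5%, 52.8%, and fold rise for B of 5.2 ± 4.0: Section 1, the 26 younger women in the 2010-2011 season.
- Benchmarks 70%, 40% and 2.5, and the Clopper-Pearson method: Section 7.4.

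**Step 1: reproduce the plan's power.** Take an exact binomial test with at most 2.5% in each tail. Under p = 0.40:
- P(X ≤ 16) = 2.21% and P(X ≤ 17) = 4.13%, so the lower cut is 16.
- P(X ≥ 33) = 1.33% and P(X ≥ 32) = 2.503%, so the upper cut is 33.

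The power is P(X ≤ 16) + P(X ≥ 33) at the assumed rate:
- H1N1 and H3N2: above 99.99%, which agrees with the stated figure of at least 99%.
- B: 3.761% + 0.694% = 4.46%, which is the stated figure.

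Only the upper tail for B means that an acceptable response is shown; the lower tail would mean concluding that B is below 40%. The chance of establishing acceptability for B is therefore 0.69%, not 4.46%.

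**Step 2: power for the named primary endpoint.** The 70% value is taken from 7.4, because 7.1 sets none. At n = 60 the lower 95% Clopper-Pearson bound is 69.6% for 49 responders and 71.5% for 50, so a bound above 70% needs X ≥ 50. A point estimate above 70% needs X ≥ 43, since 0.70 × 60 = 42.

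| Strain | Assumed rate | Lower bound > 70%: P(X ≥ 50) | Point estimate > 70%: P(X ≥ 43) |
|---|---|---|---|
| H1N1 | 92.3% | 99.4% | > 99.9% |
| H3N2 | 88.5% | 92.1% | > 99.9% |
| B | 52.8% | 0.00007% | 0.2% |

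The rate 52.8% cannot arise from 26 women (13/26 = 50.0%, 14/26 = 53.8%). At either neighbouring value the bound rule for B has a chance of at most about 0.0002%, so the result does not change.

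**Step 3: strain B under each criterion in 7.4.**

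| Criterion | Earlier value | Met? | Chance with n = 60 |
|---|---|---|---|
| Seroprotection 70% | 52.8% | no | 0.00007% (bound); 0.2% (point estimate) |
| Seroconversion 40% | 38.5% | no | 0.69% (bound, X ≥ 33); 35% (point estimate, X ≥ 25) |
| GMTR 2.5 | 5.2 | yes | about 98% (bound); > 99.9% (point estimate) |

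The GMTR chances read the quoted 4.0 as a geometric standard deviation, which the protocol does not say. On that reading the standard error of the log ratio is ln 4.0 / √60 = 0.179, and ln(5.2/2.5) / 0.179 = 4.09. The noncentral t with 59 degrees of freedom then gives 98% for a lower 95% limit above 2.5. The plain comparison of 5.2 with 2.5 needs no such reading.

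**The case against.** Three stronger readings are tempting, and the documents do not support them.

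- **That the 99% power statement is false.** It is not. Section 7.1 names seroconversion, limits the 99% to the two A strains and discloses very low power for B. The figures reproduce. They simply do not describe the primary endpoint.
- **That the protocol adopts three competing success rules.** Section 2.1 sets no threshold, 7.1 sets one test, and 7.4 reports what an external criterion specifies without adopting it. The defect is one test on a non-primary endpoint plus a cited benchmark with no stated role.
- **That the two rates give opposite verdicts for B.** They agree: both fall short on the earlier data. Only the GMTR route differs.

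It can also be said that the study is single-arm and descriptive, that 60 was chosen for precision and a minimum group size, and that exact intervals for both rates are already planned. This makes the matter less grave, but does not remove it: the same section specifies a null value, a significance level and power to establish acceptability, and gives no interval width for the primary endpoint.

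The choice between a point estimate and a confidence bound might be left to an SAP. That objection stands in part. The drop to 92.1% for H3N2 depends on choosing the bound; under a point-estimate rule both A strains exceed 99.9%. The mismatch between primary and tested endpoint is in the protocol itself and does not depend on that choice.

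**Conclusion.** The point holds as a mismatch within the protocol. The named primary endpoint has no null value, power or stated precision; the only test and power belong to an endpoint that 2.1 places among the others; and the any-of-three criterion in 7.4 has no declared function.

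For the A strains the practical effect is small. H1N1 keeps 99.4% under the stricter rule, and H3N2 has 92.1% or over 99.9% depending on the rule. For B the effect is decisive: failure is nearly certain on seroprotection against 70% and on the seroconversion bound against 40%, while success is likely if GMTR alone suffices.

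These are projections from 26 non-pregnant women in an earlier season, sampled at 3 weeks, with all 60 women evaluable. The 70% threshold is borrowed from 7.4, and the 98% for GMTR rests on the geometric standard deviation reading.

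**What to change.** Amend 7.1 and 7.4 as follows.

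1. Tie one acceptability rule per strain to Day 28 seroprotection, on a named statistic, and state its power. If the rule is a lower 95% Clopper-Pearson bound above 70% with n = 60, give 99.4% (H1N1), 92.1% (H3N2) and essentially 0% (B). If it is a point estimate above 70%, give over 99.9%, over 99.9% and 0.2%.
2. Label the seroconversion test against 40% as secondary. Keep its power for the A strains, and give the chance of establishing acceptability for B as 0.69%, explaining that the 4.46% includes 3.76 points for concluding that B is below 40%.
3. State that the CPMP criteria are reported descriptively for each strain and are not an alternative route to success.
4. Use one seroprotection cut-off in 2.1 and 7.4.

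The cost is wording only, with no extra patients. The downside is that the stated power becomes less favourable for B, and for H3N2 if the bound rule is chosen.

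### Section 7.1's 4.46% power for strain B adds both rejection tails; the power to establish acceptable seroconversion is 0.7% (exact)

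*Protocol*

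**What the plan says.** Protocol section 7.1 first rests the sample size of 60 on the expected precision of the 95% confidence intervals and on a European recommendation of at least 50 subjects per group. It then adds a test with a stated purpose, "For establishing the acceptability of the antibody response to H1N1, H3N2, and B for AdimFlu-S": the three seroconversion rates "will be tested against a 40% lower bound for adult subjects".

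The assumed rates come from non-pregnant women vaccinated in the 2010-2011 season. For the first strain, "the seroconversion rates were 84.6% against influenza A/H1N1 virus"; for the other two they were "80.8% against influenza A/H3N2 virus and 38.5% against influenza B virus". The number analysed is fixed by "Given 60 female subjects who receive AdimFlu-S will be evaluable for antibody titers". From these inputs the section concludes that there is at least 99% "power to establish an acceptable seroconversion for A/H1N1 and A/H3N2, and 4.46% for B with 5% two-sided significance level".

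Section 7.4 specifies exact Clopper-Pearson 95% intervals for the seroprotection and seroconversion rates. It also cites the European criteria: 70% seroprotection, 40% seroconversion or a titre ratio of 2.5, joined by the word or.

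**The concern.** The assumed rate for B, 38.5%, is below the 40% that the test is meant to exceed. The chance that a test shows a rate to be above a bound rises with the true rate. At a true rate below the bound, it must therefore be smaller than the error rate allowed in that direction. A two-sided 5% level allows 2.5% in each direction. A power of 4.46% to establish acceptability is thus impossible on the section's own inputs, which suggests that both tails were counted.

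What is at stake is what the number means. A reader of section 7.1 takes 4.46% as the chance that B will be shown acceptable on seroconversion. If most of it is the chance that B will be shown to be significantly below 40%, the protocol states a power that the design does not have. It also leaves unsaid that its own assumption puts B on the wrong side of the bound.

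**Working it through.** **Inputs, all from section 7.1:** n = 60 evaluable; bound p0 = 0.40; assumed B rate p1 = 0.385; two-sided 5%, taken as 2.5% per tail. X is the number who seroconvert, binomial with n = 60.

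**Step 1: rejection region of the exact equal-tailed test at p0 = 0.40.**
- Upper tail: P(X ≥ 33) = 1.33%. P(X ≥ 32) = 2.503%, just over 2.5%. The test rejects upward from 33.
- Lower tail: P(X ≤ 16) = 2.21%. P(X ≤ 17) = 4.13%, too large. The test rejects downward at 16 or fewer.

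**Step 2: reproduce the stated figure at p1 = 0.385.**
- P(X ≥ 33) = 0.694%
- P(X ≤ 16) = 3.761%
- Sum = 4.455% (unrounded 4.4553%), which rounds to the stated 4.46%.

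Moving p1 within its rounding, from 0.3845 to 0.3855, takes the sum from 4.50% to 4.41%, so the match is with 0.385 as printed.

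**Step 3: try upward-only readings.** None gives 4.46%.

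| Reading | Result for B |
|---|---|
| Exact, 2.5% upper tail (X ≥ 33) | 0.7% |
| Score test, 2.5% upper tail (X ≥ 32) | 1.4% |
| Normal or arcsine approximation, 2.5% upper tail | about 1.35% to 1.4% |
| Exact, one-sided 5% (X ≥ 31) | 2.6% |
| Observed rate merely above 40% (X ≥ 25), no test | about 35% |

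**Step 4: split the stated figure by direction.**
- Upper tail, rate shown above 40%: 0.694 / 4.455 = 16%.
- Lower tail, rate shown below 40%: 3.761 / 4.455 = 84%.

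**Step 5: compare with the interval in section 7.4.** The Clopper-Pearson lower 95% limit is 39.996% at 32/60 and 41.6% at 33/60. It exceeds 40% only from 33 upward, the same cut-off as in step 1. The power to place that limit above 40% is therefore 0.69%.

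**Step 6: check the A strains.** At 84.6% and 80.8% the lower tail is negligible and the upper-tail power exceeds 99.9%. The statement of at least 99% is correct. Counting both tails does harm only for B, because only B is assumed to lie below the bound.

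**The case against.** The strongest reply is that nothing rests on this number. The study is descriptive, and 60 was chosen for precision and the 50-per-group recommendation; the power sentence follows from 60 and does not justify it. The protocol prints 38.5% beside a 40% bound and declares power below 5%, so no reader would expect the B test to succeed. Moving from 4.46% to 0.7% changes no decision about size, endpoint or conduct. This stands, and it limits the severity. It does not make the figure right, since the section names the claim and the number is not the power for that claim.

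A second reply is that section 7.1 names no test, so 0.69% is not the only possible value. This also stands. The exact test is inferred because it reproduces the printed figure and agrees with the interval in section 7.4. A continuity-corrected Wald test has the same rejection region, and a score test would give about 1.4%. The conclusion is the same throughout that range.

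A reader might infer more than the document supports:
- **That a three-strain claim is almost certain to fail.** Section 7.1 gives power strain by strain, and no joint success rule is defined.
- **That B cannot be found acceptable.** Section 7.4 lists seroconversion as one of three alternative criteria, and the Introduction reports a B fold rise of 5.2 in 26 women aged 18 to 40, against the criterion of 2.5. The primary endpoint in section 2.1 is seroprotection, not seroconversion.
- **That the B test must be withdrawn or the study enlarged.** Low power at a rate taken from 26 non-pregnant women does not invalidate a pre-stated test. Whether to keep it is the sponsor's choice.

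**Conclusion.** The point holds as a correction to a stated power. The 4.46% for B is a two-tailed rejection probability, and only 0.69 percentage points of it correspond to establishing acceptable seroconversion. On the section's own inputs the power is 0.7% with the exact test and about 1.4% with a score or normal-approximation test. It cannot exceed 2.5% while the assumed rate is below the bound. The overstatement is about 3.8 percentage points (4.46 − 0.69 = 3.77).

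This rests on 60 evaluable subjects, a true B rate of 38.5%, a two-sided 5% level split equally, and the exact test as the one the protocol used. The severity is minor to moderate: the figure is wrong for its stated purpose, but the printed value already signals near-zero power and the sample size does not depend on it. It would be too strong to say that the protocol hides a likely failure or that its sample size is unsound.

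**What to change.** In section 7.1, replace 4.46% with the upper-tail power: 0.7%, defined as the probability that the lower exact (Clopper-Pearson) 95% limit exceeds 40% with 60 evaluable subjects and a true rate of 38.5%. If a score test is the intended analysis, name it and give about 1.4%.

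Add one sentence saying that the assumed B rate lies below the 40% bound, so the study is not powered to establish acceptability for B on the seroconversion criterion.

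Leave the A-strain statement, the sample size of 60 and the planned analysis of B unchanged. No joint three-strain power is needed. The cost is a change to two sentences, with no effect on recruitment, procedures or analysis; the stated figure for B becomes less favourable.
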